### Statistical analysis

All analyses will be performed with STATA statistics software, version 11.0 (STATA Corporation, College Station, EUA). Kolmogorov-Smirnov test will be used to assess normality of data. Quantitative and normally distributed parameters will be expressed as mean + standard deviation. Quantitative and non-normally distributed data will be shown as median and interquartiles. Analysis of variance (ANOVA) test will be used for comparing the values between and within groups. Analysis of covariance (ANCOVA) will be used to identify any differences between the four groups at the end of study, adjusting for baseline values and covariates (such as dietary intake, physical activity, and sun exposure). Bonferroni will be used to pairwise comparisons for the values after the intervention.

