### Participants

Participants will comprise 100 patients with stage II or III CRC. The inclusion criteria will consist of: patients with stage II or III CRC if they have to begin chemotherapy; aged > 18 years; BMI range of 18.5–30 kg/m^2^; serum 25(OH)D < 30 ng/ml; not having autoimmune disease, diabetes, hypertension, or renal, hepatic, parathyroid, and gastrointestinal disorders; not taking vitamin D and/or omeaga-3 supplements and other vitamin/mineral supplements or parenteral nutrition; not taking laxative and/or anti-inflammatory medications; not allergic to fish and fish products; and without history of having other cancers. Exclusion criteria will consist of: affected by any acute disease during the study; changes to the chemotherapy plan; refusal to continue with chemotherapy; unwilling to continue the study; also, we will exclude patients who were less than 90% compliant with treatment.

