### Randomization and blinding

The randomization assignment will be performed using computer-generated random numbers. The 100 participants who meet the criteria will be randomly allocated into four groups: 1) a 50,000 IU vitamin D soft gel (weekly) plus 2 omega-3 fatty acid capsules (daily), each capsule containing 330 mg omega-3 fatty acid; 2) a 50,000 IU vitamin D soft gel (weekly) plus 2 omega-3 fatty acid placebo (daily); 3) a vitamin D placebo (weekly) plus 2 omega-3 fatty acid capsules (each capsule containing 330 mg omega-3 fatty acid); and 4) a vitamin D placebo (weekly) plus 2 omega-3 fatty acid placebo (daily). Each omega-3 fatty acid capsule (MorDHA VISION, Minami Nutrition, Belgium) contains 54 mg EPA, 250 mg DHA, and 26 mg of other omega-3 fatty acids. The 50,000 IU vitamin D soft gels are supplied by Zahravi, Iran. The vitamin D and omega-3 fatty acid placebo contain oral paraffin and corn oil, respectively, are supplied by Zahravi, Iran, and are carefully matched in appearance with vitamin D and omega-3 fatty acid soft gels. Patients will receive verbal and written counseling on how to consume the capsules. Compliance will be evaluated by capsule count every 2 weeks. The supplementation will begin before the first session of chemotherapy.

For blinding, a person not involved in the study protocol will create the randomization list, assigning participants to the vitamin D, omega-3, co-supplementation, or placebo group. Vitamin D, omega-3, and placebo tablets will be placed into unlabeled identical containers. The study leader will label these containers with participant numbers using the randomization list. All investigators and participants will be blinded to the random assignments.

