### Measurements

A questionnaire about patients’ medications, diseases, cancer history, and probable supplement use will be recorded at the beginning of the intervention. Dietary intake will be evaluated by 3-day, 24-h record questionnaires (two week days and one weekend day) at baseline and the end of the intervention, and total energy, macronutrient, and some micronutrient (vitamins A, D, E; calcium and selenium) intake will be estimated using nutritionist IV software. To evaluate physical activity levels the short form of the international physical activity questionnaire (IPAQ) [27] will be used at baseline and the end of the intervention. Sun exposure will be assessed with the questionnaire [28] at baseline and the end of the study. A sunshine exposure score is obtained based on (a) how often and what time of day the subjects are outside, (b) which parts of the body are exposed as a percentage of total body surface area, and (c) do the subjects use sun screen or not. Anthropometric indices will be measured after overnight fasting, with minimal clothing and without shoes, before and after the intervention. Body weight will be measured to an accuracy of 0.1 kg using a Beurer scale (Beurer, Germany). Height will be assessed to the nearest 0.5 cm in the standing position without shoes. BMI will be computed as body weight (kg) divided by height squared (cm^2^). A bioelectric impedance analyzer (Quad scan 4000; Body stat) will be used to measure total body fat and fat free mass percentage. The difference in CRP/albumin levels, as an indicator of nutritional status, between groups will also be compared with score values proposed by Correa et al.: no risk ≤ 0.4; low risk = 0.4–1.2; medium risk = 1.2–2; high risk ≥ 2.0 [29]. This indicator will be assessed at baseline and end of the intervention.

Before and after the intervention, blood samples will be collected after 12-h overnight fasting. The serum of patients will be kept at − 80 °C until biochemical analyses. Serum 25(OH)D will be measured by enzyme-linked immunosorbent assay (ELISA) and Euro Immun kit (Euro Immun, Germany). Serum TNF-α, IL-1β, IL-6, and IL-8 levels will be assessed by ELISA and Bender Med kit (Bender Med, Germany). Serum CRP and albumin will be determined by ELISA and Binding kit (Binding, UK). Tumor marker CEA will be evaluated by ELISA and CanAg kit (CanAg, Italy).

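### ANOVA within and between groups is planned beside baseline-adjusted ANCOVA, and nothing says that ANCOVA alone carries the conclusion on treatment effect

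*Protocol article*

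**What the plan says.** The Statistical analysis section names three inferential steps.

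- The first is an ANOVA with two uses: "Analysis of variance (ANOVA) test will be used for comparing the values between and within groups". No adjustment is mentioned for it.
- The second is a baseline-adjusted comparison of the arms: "Analysis of covariance (ANCOVA) will be used to identify any differences between the four groups at the end of study, adjusting for baseline values". Diet, activity level and exposure to sun are given as examples of further covariates.
- The third concerns pairs of arms: "Bonferroni will be used to pairwise comparisons for the values after the intervention". The text does not say whether these follow the ANOVA or the ANCOVA, and it names no correction for the within-group tests.

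The Measurements section gives two time points: "Before and after the intervention, blood samples will be collected after 12-h overnight fasting". Under Randomization and blinding, the allocation is stated as "The 100 participants who meet the criteria will be randomly allocated into four groups". The same section places the start of treatment relative to chemotherapy: "The supplementation will begin before the first session of chemotherapy". The objectives section expects the measured variables to improve and names no comparator.

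**The concern.** With one measurement before and one after the intervention, comparing values within groups most naturally means a before-after test in each arm. Such a test asks whether the arm changed. It does not ask whether the arm changed more than placebo. All four arms begin chemotherapy between the two blood samples, so inflammatory markers, CEA or body composition could move in every arm whatever capsule is taken. If one active arm crosses p < 0.05 and placebo just fails to, the pattern looks like a supplement effect but is not evidence of one.

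There is a second, smaller issue. The same between-arm hypothesis is tested by unadjusted ANOVA and by ANCOVA. The two can disagree, and the text does not say which result then stands.

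**Working it through.** **Inputs.** From the protocol article: four arms, 20 evaluable patients per arm and alpha 0.05 (Sample size), two time points (Measurements). Assumed, because the article gives neither: correlation between baseline and week 8 of 0.3, 0.5 or 0.7, and a shift common to all arms of 0, 0.25 or 0.5 SD. Supplement effect: none.

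**The plan's own figure.** The 20 per group cannot be reproduced, because the TNF-α difference is not stated. It is used here only as the arm size. The attrition step is consistent: 20/(1 − 0.20) = 25.

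**Step 1: one within-arm test.** The change has SD √(2(1 − ρ)) in units of the outcome SD. The paired t test on 19 degrees of freedom therefore has noncentrality shift × √20 / √(2(1 − ρ)). Its probability of significance, p, follows from the noncentral t distribution.

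**Step 2: misleading patterns.** The arms are independent and share the same p.

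- A given active arm significant, placebo not: p(1 − p).
- At least one of three active arms significant, placebo not: (1 − p)[1 − (1 − p)³].

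| Correlation | Shared shift | p | Given arm | Any of three |
|---|---|---|---|---|
| any | 0 | 5.0% | 4.8% | 13.5% |
| 0.3 | 0.25 SD | 14.6% | 12.5% | 32.2% |
| 0.3 | 0.5 SD | 43.4% | 24.6% | 46.3% |
| 0.5 | 0.25 SD | 18.6% | 15.1% | 37.5% |
| 0.5 | 0.5 SD | 56.5% | 24.6% | 40.0% |
| 0.7 | 0.25 SD | 27.8% | 20.1% | 45.0% |
| 0.7 | 0.5 SD | 78.2% | 17.1% | 21.6% |

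Simulation (6,000 null trials per setting) agrees: about 5% and 13% with no shift, and 12% to 25% and 21% to 47% with one.

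**Step 3: ceilings.** p(1 − p) is largest at p = 0.5, where it is 25%. With q = 1 − p, the second pattern is q − q⁴. It is largest where 4q³ = 1, so q = 0.630, and its value there is 0.630 × 0.75 = 47.2%. No shift or correlation can exceed these values.

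**Step 4: any significant arm.** With no shared shift, the chance that at least one of the four within-arm tests is significant is 1 − 0.95⁴ = 18.5% per outcome.

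**Step 5: two between-arm tests.** In the same simulated null trials, ANOVA alone rejects in 4.5% to 5.6% and ANCOVA alone in 4.6% to 5.5%. Both agree with 5% within simulation error. At least one of the two rejects in 6.1% to 8.6%, and the figure rises with the correlation. A separate run of 20,000 trials per setting gave 6.6%, 7.5% and 8.5% at correlations 0.3, 0.5 and 0.7.

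**Step 6: the other reading of the sentence.** If a repeated-measures ANOVA is meant, its group-by-time test with two time points equals an ANOVA of the change. That test beside ANCOVA, with either allowed to count, rejects in about 7% to 8% of null trials over the same correlations.

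**The case against.** The strongest reply is that the plan already gives the treatment question to one method: "Analysis of covariance (ANCOVA) will be used to identify any differences between the four groups at the end of study". No sentence says that efficacy will be claimed from a within-arm test, and a condensed article may leave the order of analyses to an analysis plan. This is fair, and it rules out a stronger reading. A reader might infer that the trial means to claim effects without a valid randomised comparison. The documents do not support that. What remains is that the article itself plans the additional tests and does not limit what they may support.

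A reader might also infer that the unadjusted between-arm ANOVA is invalid. It is not: it is a randomised comparison with about 5% error. The fault lies only in having two unranked tests, and the cost arises only if either may be reported as the result.

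The word *within* may mean a repeated-measures ANOVA, which keeps the pairing and contains a valid randomised test. The wording does not exclude this. It removes the within-arm issue if the group-by-time term is the one reported, but two between-arm tests remain. There is no textual basis for saying that the pairing will be ignored.

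Two further extensions do not stand. The 25% and 47% figures are mathematical ceilings and should not be read as expected rates, since the article gives no size or direction for a shared shift. And selection on "serum 25(OH)D < 30 ng/ml" implies regression to the mean for 25(OH)D. It has not been shown for the cytokines, CEA, CRP/albumin or body composition.

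**Conclusion.** The concern holds in a limited form. The plan includes within-group testing and an unadjusted between-arm test beside the ANCOVA, and it does not state that the ANCOVA alone supports conclusions about the supplements.

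Read as before-after tests, the within-group comparisons cannot separate a supplement effect from a change that all arms share once chemotherapy starts. When the supplements do nothing, the misleading contrast with placebo appears in about 5% of trials for a given active arm with no shared change, and in at most 25% with one. For any of three active arms it appears in about 13% and at most 47%. The choice between two between-arm tests raises the error per outcome from 5% to about 6% to 9%.

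These figures assume normal data, equal variances, 20 per arm, and the correlations and shifts shown. They are per outcome. They should not be multiplied over the outcome list, because the shared change may differ from one outcome to another.

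**What to change.** Replace the ANOVA sentence with:

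> *For each outcome, claims about treatment effect rest only on the between-arm ANCOVA of the week-8 value adjusted for its baseline and the planned covariates, with Bonferroni-adjusted pairwise comparisons taken from that model. Within-arm changes and unadjusted group values are described with 95% CIs, without p-values.*

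This keeps the planned covariates and pairwise comparisons and settles which model the pairwise comparisons come from. The secondary analysis of 25(OH)D change against other variables is unaffected. With the ANCOVA as the single between-arm test, the simulated overall error per outcome is 4.6% to 5.5%, in line with the nominal 5%. The change needs no new data and no change in sample size. Its cost is fewer p-values to report.

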## Methods/design

### Design

We will conduct an 8-week, double-blind randomized controlled trial in a factorial design. This trial will be conducted at the oncology clinic of Tehran Gastroenterology & Hepatology Center (TGHC), Iran for 8 weeks to evaluate the effects of vitamin D_3_ (50,000 IU weekly) and omega-3 fatty acids (660 mg daily) co-supplementation on inflammatory biomarkers, tumor marker CEA, and nutritional status in patients with CRC (Figs. 1 and 2). The protocol is written in line with the Standard Protocol Items: Recommendations for Interventional Trials (SPIRIT) checklist (Additional file 1).

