### Objectives and hypotheses of the study

The primary objective of the present study is to assess the impact of 8-week vitamin D_3_ and omega-3 fatty acids co-supplementation on serum 25(OH)D, inflammatory biomarkers, CRP/albumin, tumor marker CEA, body mass index (BMI), and body composition in patients with stage ӀӀ or ӀӀӀ CRC undergoing chemotherapy. As a second objective, the study will also evaluate the relationship between alterations in 25(OH)D levels and other variables. It is also expected that there will be improvement in evaluated variables.

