### Sample size

The number of participants was calculated according to the alterations in TNF-α between the control and co-supplementation groups and based on the study conducted by Mohammadzadeh et al. [25]. It was calculated with the use of fixed factor levels model (determining sample size for analysis of variance) [26] and considering sigma (standard deviation of TNF-α) of 1.25, 90% power, α of 0.05, resulting in 20 patients for each group. To allow for attrition, 25 patients will be recruited for each group. Collectively, a sample of 100 patients with stage II or III CRC will be enrolled.

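### The trial is declared a 2x2 factorial, but the analysis names no main effect and no interaction, and spreads alpha over pairs outside the stated aim

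*Protocol article*

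**What the plan says.** - **Design** (Protocol article, Design): "We will conduct an 8-week, double-blind randomized controlled trial in a factorial design".
- **Arms** (Randomization and blinding): "The 100 participants who meet the criteria will be randomly allocated into four groups". The four are vitamin D or its placebo crossed with omega-3 or its placebo, which is a 2x2 layout.
- **Aim** (Objectives and hypotheses): "The primary objective of the present study is to assess the impact of 8-week vitamin D_3_ and omega-3 fatty acids co-supplementation" on a list of outcomes that includes inflammatory biomarkers.
- **Sizing** (Sample size): "The number of participants was calculated according to the alterations in TNF-α between the control and co-supplementation groups", using a "fixed factor levels model (determining sample size for analysis of variance" method with SD 1.25, 90% power and α 0.05. This gives 20 per group, raised to 25 for attrition. The TNF-α difference itself is not given.
- **Analysis** (Statistical analysis): "Analysis of covariance (ANCOVA) will be used to identify any differences between the four groups at the end of study", adjusted for baseline and covariates, and then "Bonferroni will be used to pairwise comparisons for the values after the intervention". The section mentions no vitamin D factor, omega-3 factor, marginal comparison or interaction.

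**The concern.** A factorial layout has two advantages over four parallel arms. Every patient contributes to the estimate for each supplement, and the data show whether the combination differs from the sum of its parts. The stated analysis uses neither.

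A 3-df test across four groups does not say which supplement is responsible for a difference. The pairwise step compares one cell with another and so uses half the available patients for each supplement. If all pairs are tested, part of the alpha goes to comparisons such as vitamin D alone versus omega-3 alone, which no objective asks for. The comparison named for sizing is treated as one pair among several, and the reader cannot tell whether the 90% belongs to that comparison or to the four-group test.

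**Working it through.** **Inputs.** From Sample size: 20 evaluable per group (25 recruited), SD 1.25, power 90%, α 0.05, taken as two-sided. Not stated: the TNF-α difference and the number of pairs. All pairs of four groups would be 4×3/2 = 6, so α = 0.05/6 = 0.0083. Three comparisons against double placebo would give 0.05/3. Baseline adjustment is ignored throughout.

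**1. The plan's own figure.** With no difference stated, n = 20 cannot be derived and can only be solved backwards. For a four-group F test with 3 and 76 df, where the extreme groups differ by Δ and the others lie midway, the noncentrality is n(Δ/σ)²/2. At n = 20, power is 90% when Δ/σ = 1.22 (20 × 1.2216²/2 = 14.9), that is Δ = 1.2216 × 1.25 = 1.53. A rounder Δ/σ = 1.25 also gives n = 20, with 91.4% power.

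**2. Standard errors in SD units, n = 20 per cell, 76 df.**
- Pair, 20 vs 20: √(2/20) = 0.316
- Main effect, 40 vs 40: √(1/20) = 0.224
- Interaction, difference of differences: √(4/20) = 0.447

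**3. One supplement.** Assume each adds 1.22/2 = 0.61 SD with no interaction. This is also the pattern behind step 1: double placebo at 0, the single supplements at 0.61, the combination at 1.22. Noncentrality is 0.611/0.316 = 1.93 for a pair and 0.611/0.224 = 2.73 for a main effect. Noncentral t gives:

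| Alpha | Pair (20 vs 20) | Main effect (40 vs 40) |
|---|---|---|
| 0.05/6 | 23% | 51% |
| 0.05/3 | 31% | 61% |
| 0.05/2 | – | 67% |
| 0.05 | 48% | 77% |

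The gap from 23% to 77% is 54 points. Moving to the margins at the same alpha gives 51 − 23 = 28 points, and relaxing alpha gives the other 77 − 51 = 26. With all 25 per cell retained, the extremes are 30% and 86%.

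The size of the gap depends on the effect. For main effect at 0.05 against a six-way pair, with 20 per cell:
- 0.5 SD: 60% vs 14%
- 0.8 SD: 94% vs 43%
- 1.22 SD from one supplement alone: above 99.9% vs 87%

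**4. Co-supplementation vs double placebo at 1.22 SD.** Noncentrality is 1.2216/0.316 = 3.86. Power is 87% at 0.05/6, 92% at 0.05/3 and 97% as one planned contrast at 0.05. With 25 per cell and six pairs it is 95%.

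**5. Interaction.** At 0.61 SD, noncentrality is 0.611/0.447 = 1.37 and power at 0.05 is 27%. Reaching 90% would take an interaction of 1.47 SD, or 1.47 × 1.25 = 1.84 TNF-α units.

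**The case against.** The stated aim is co-supplementation, and the pairwise step tests it directly. No objective asks for a marginal effect or for synergy. Simple comparisons are defensible when the combination is the question, and margins mislead if the supplements interact. A four-group ANCOVA and a two-factor ANCOVA with interaction are also the same fitted model; only the contrasts differ. All of this stands. It is why the primary contrast should stay a two-cell comparison and the main effects should be secondary. It does not explain why a declared factorial has no factorial contrast, or why alpha goes to pairs outside the aim. An unseen analysis plan could hold more, but the article does state its model and multiplicity rule, and these do not follow the design.

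Three stronger readings are tempting, and the document does not support them.
- **That neither supplement's effect is ever estimated.** The pairs include each supplement alone against double placebo, so both simple effects are estimated. What is absent is the marginal effect and the interaction.
- **That the factorial structure alone accounts for the loss of power.** About half of the gap in step 3 is the Bonferroni correction. For the interaction nothing is lost: it is not tested, and it would be poorly powered under any analysis.
- **That the sized comparison falls below its stated 90%.** The 87% needs a back-solved effect, six pairs and exactly 20 evaluable per cell. Three pairs give 92%, and 25 per cell gives 95%. Baseline adjustment could raise power further.

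**Conclusion.** The point holds as a mismatch between the declared design and the stated analysis. The plan reaches its primary comparison and both simple effects. It leaves out the marginal main effects and the interaction, which the 2x2 layout makes available at no extra cost, and it spends alpha on comparisons outside its aim.

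Under the additive half-and-half assumption with 20 per cell, testing one supplement as a six-way Bonferroni pair has 23% power. The factorial margin has 51% at the same alpha and 67% at 0.025. Making the sized comparison a single planned contrast moves it from 87% to 97%, entirely through alpha. These figures rest on the back-solved 1.22 SD, six pairs, no interaction and no gain from baseline adjustment. The mismatch itself rests on none of them.

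**What to change.** Replace the between-group text in Statistical analysis with one ANCOVA per outcome containing vitamin D (yes/no), omega-3 (yes/no), their interaction and the baseline value. Then fix the contrasts before unblinding:

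1. **Primary:** co-supplementation vs double placebo on TNF-α, one contrast at α 0.05, not conditional on the four-group test.
2. **Secondary:** the vitamin D and omega-3 main effects, averaged over the other factor. Test them only after the primary contrast succeeds, or at 0.025 each. Simply dropping Bonferroni would leave three tests with no error control.
3. **Interaction:** an estimate with 95% CI, its low power stated (27% at 0.61 SD), and no claim that synergy is absent from a non-significant test.
4. **Display:** the four cell means beside the main effects, because a main effect is a clean average only if the interaction is small.

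In Sample size, state the TNF-α difference assumed and which test the 90% refers to.

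The cost is a change of wording and of contrast statements, with no extra patients or measurements. With 0/1 coding and an interaction term, the printed vitamin D coefficient is the simple effect without omega-3, so the main effect has to be requested as an explicit averaged contrast.

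### For serum 25(OH)D, one residual variance pooled over the four arms would miscalibrate the two omega-3 comparisons within vitamin D strata if, as is plausible, the spread is larger under vitamin D

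*Protocol article*

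**What the plan says.** The Statistical analysis section of the protocol article makes no distinction between outcomes. It states: "Analysis of variance (ANOVA) test will be used for comparing the values between and within groups". For end-of-study values: "Analysis of covariance (ANCOVA) will be used to identify any differences between the four groups at the end of study", adjusted for baseline and for covariates such as diet, physical activity and sun exposure. Then: "Bonferroni will be used to pairwise comparisons for the values after the intervention". The only distributional check named is the Kolmogorov-Smirnov test of normality. No check of equal variances and no unequal-variance method is mentioned.

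The Objectives section puts serum 25(OH)D first in the primary objective: "co-supplementation on serum 25(OH)D, inflammatory biomarkers, CRP/albumin, tumor marker CEA, body mass index (BMI), and body composition".

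Under Randomization and blinding: "The 100 participants who meet the criteria will be randomly allocated into four groups". Two of these groups receive vitamin D weekly. The other two receive its placebo, one of them being "a vitamin D placebo (weekly) plus 2 omega-3 fatty acid capsules". Under Participants, entry requires "serum 25(OH)D < 30 ng/ml". No SD of 25(OH)D, before or after treatment, is given anywhere.

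**The concern.** Ordinary ANOVA and ANCOVA estimate one residual variance and use it for every pairwise contrast. That is safe when the arms have similar spread. 25(OH)D is the outcome for which this is least assured, because it measures the substance given to half the patients. Everyone starts in a range capped at 30 ng/ml. Two arms are then supplemented for 8 weeks, and any variation in individual response adds to their spread but not to that of the other two arms.

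With equal arm sizes the pooled variance is the average of the arm variances. If the vitamin D arms are more variable, this average is too small for the comparison between them and too large for the comparison between the two arms without vitamin D. The data can be perfectly normal and the problem remains, so the planned normality test would not reveal it.

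At stake are the intervals and p-values for the two simple effects of omega-3 on 25(OH)D: co-supplementation vs vitamin D alone, and omega-3 vs placebo. The first shows whether adding omega-3 changes the 25(OH)D response to vitamin D.

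**Working it through.** **Inputs from the document.** Four arms; 20 evaluable and 25 recruited per arm (Sample size section); α 0.05. Four arms give 4 × 3 / 2 = 6 pairs, so Bonferroni tests each at 0.05 / 6 = 0.0083.

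**Assumptions.** r is the SD of end-of-study 25(OH)D in the vitamin D arms divided by that in the other arms. The document does not give it, so it is varied from 1 to 3. With baseline adjustment, a slope of 0.5 on baseline (baseline SD 1) is also assumed.

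**The plan's own figure.** The only calculation in the plan is for TNF-α: 20 per arm, raised to 25 (20 / (1 − 0.20) = 25) and 100 in total (4 × 25). It is internally consistent on attrition and does not involve 25(OH)D.

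**Is r > 1 plausible?** If individual response varies independently of the untreated level, the response SD needed, in units of the placebo-arm SD, is √(r² − 1). This is √(1.25² − 1) = 0.75 for r = 1.25 and √(1.5² − 1) = 1.12 for r = 1.5. That is plausible, but the document cannot confirm it.

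**Standard errors without baseline adjustment.** The pooled variance is (r² + 1)/2. Pooled SE over true SE is √((r² + 1)/2)/r for the vitamin D pair and √((r² + 1)/2) for the other pair. At r = 2: √2.5 / 2 = 0.79, and √2.5 = 1.58.

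**Standard errors with slope 0.5.** Residual variances are r² − 0.25 and 1 − 0.25 = 0.75, with average (r² + 0.5)/2. At r = 2: √(2.25/3.75) = 0.77, and √(2.25/0.75) = 1.73.

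| r | D pair, unadjusted | D pair, slope 0.5 | Non-D pair, unadjusted | Non-D pair, slope 0.5 |
|---|---|---|---|---|
| 1 | 1.00 | 1.00 | 1.00 | 1.00 |
| 1.25 | 0.91 | 0.89 | 1.13 | 1.17 |
| 1.5 | 0.85 | 0.83 | 1.28 | 1.35 |
| 2 | 0.79 | 0.77 | 1.58 | 1.73 |
| 3 | 0.75 | 0.74 | 2.24 | 2.52 |

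**Error rates.** Simulated baseline-adjusted ANCOVA, 20 per arm, slope 0.5, no omega-3 effect, each pair tested at 0.0083:

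| r | Co-supplementation vs vitamin D alone, pooled | Omega-3 vs placebo, pooled |
|---|---|---|
| 1 | 0.008 | 0.008 |
| 1.25 | 0.021 | 0.002 |
| 1.5 | 0.027 | 0.001 |
| 2 | 0.040 | no rejections |
| 3 | 0.050 | no rejections |

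With HC3 standard errors the vitamin D pair runs at 0.007 to 0.011 throughout.

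**Coverage.** For an unadjusted 95% interval with 25 per arm and no baseline covariate, the simulated error for the vitamin D pair is 0.078, 0.096, 0.125 and 0.145 at r = 1.25, 1.5, 2 and 3. Coverage is therefore about 92%, 90%, 88% and 86%. Welch intervals, with a separate variance for each arm, keep the error at about 0.05.

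**Mixed pairs.** For a vitamin D arm against a non-vitamin-D arm, the true variance is proportional to the average of the two arm variances, which in balanced arms is the pooled value. The simulated error stays near nominal: 0.049 to 0.053 at 0.05, and about 0.008 to 0.009 at 0.0083.

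**Family-wise error.** If vitamin D raises 25(OH)D, only the two within-stratum pairs can be true nulls. The chance of any false positive over both is 0.016, 0.027, 0.040 and 0.047 at r = 1, 1.5, 2 and 3 with 20 per arm, and 0.018, 0.028, 0.040 and 0.053 with 25 per arm.

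**The case against.** Four points can fairly be made for the plan.

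- **The unequal spread is not documented.** A reader might infer that the design itself guarantees wrong error bars. It does not. No 25(OH)D SD is given, the 30 ng/ml limit applies at entry only, and the plan itself remeasures sun exposure and diet, so levels in the arms without vitamin D may also move. At r = 1 there is no distortion, and at r < 1 the direction reverses. This stands, so the point is conditional.
- **The false-positive risk is easily overstated.** A reader might infer a three- to six-fold inflation of the trial's error from 0.027 to 0.050 against 0.0083. Bonferroni protects the family of pairs, and one of the two possible null pairs becomes very conservative. Family-wise error stays at about 5% even at r = 3. This also stands. What remains is coverage and the calibration of each pair's p-value.
- **The target is narrow.** Two of six pairs on one outcome are affected, and no stated hypothesis concerns omega-3 acting on 25(OH)D. The comparisons that carry the vitamin D effect are about right. In balanced arms the pooled variance is also right for the omega-3 main effect averaged over vitamin D. This stands and limits the importance. It does not remove the point, because the plan calls for pairwise comparisons and 25(OH)D is in the primary objective.
- **The variance estimator could be left to an analysis plan.** The article does not rule out robust errors. But it chooses ANCOVA with Bonferroni pairs for every outcome and names no alternative, and the usual default of that choice is the pooled variance. This objection stands only in part.

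**Conclusion.** The point holds as a conditional, minor one. If end-of-study 25(OH)D is more variable under vitamin D, the planned analysis gives too short an interval for co-supplementation vs vitamin D alone and too wide an interval for omega-3 vs placebo. For assumed SD ratios of 1.25 to 3 and an assumed baseline slope of 0.5, the per-pair error for the vitamin D pair is about 0.02 to 0.05 instead of 0.0083. Its standard error is understated by about 11% to 26%. The standard error for omega-3 vs placebo is overstated by about 17% to 152%, or 13% to 124% without the baseline covariate.

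The document does not support three stronger readings: that the vitamin D effect on 25(OH)D would be tested wrongly, that the trial's overall error is out of control, or that the TNF-α sample size is affected. The harm is to interval coverage and p-values for the two omega-3 comparisons within vitamin D strata.

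**What to change.** In the Statistical analysis section, add one sentence: for serum 25(OH)D, between-arm contrasts in the same baseline-adjusted ANCOVA will use HC3 robust standard errors (or arm-specific residual variances), and the reported confidence intervals and Bonferroni-adjusted p-values will come from these. The choice should be fixed in advance rather than made to depend on a test of equal variances. It also covers the case where the spread is smaller under vitamin D.

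The cost is one sentence and one model option, with no new data and no change to the sample size. If the variances are in fact equal, the loss of efficiency is negligible: the simulated per-pair error with HC3 at ratio 1 is about 0.007, against the nominal 0.0083.
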